### Data management and confidentiality

Types of data collected in this study will include participant information on demography, medical and family history, health behaviours including dietary intake and micronutrient supplementation, physical activity, smoking, alcohol use, and metabolic biomarkers. All data will be de-identified in the research dataset. All anonymised data will be stored on a password protected computer. No identifiable data will be included in the final publication. All records will be kept in line with applicable national laws and regulations.

### Ethics

This study has been approved by King’s College London. Study Reference: HR-19/20-13583.

## Discussion

The health of the mother before conception can profoundly influence the risk of complications in pregnancy and may adversely affect the lifelong health of the child [17]. We have found in a large-scale survey that UK women are not adequately prepared for pregnancy. There is no easy way to identify women planning pregnancy and few NHS services to support positive lifestyle behaviour modifications despite enormous demand for advice by this demographic. In addition, targeting women with modifiable risk factors before pregnancy may be a more efficient and beneficial approach.

This study will determine whether it is achievable to link digital tools to identify high risk women planning a pregnancy with a preconception health optimisation programme. Examining change in health behaviours and biomarkers of metabolic health pre- and post-a personalised intervention will determine whether this strategy can improve health in high risk women in the preconception period.

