Achieving readiness for pregnancy through appropriate preconception planning is key to optimising pregnancy outcomes for all women, with important consequences for maternal and child health. Surveys undertaken using the London Measure of Unplanned Pregnancy (LMUP) questionnaire suggest that pregnancy planning is common [8–10], although, currently, few NHS services target women planning pregnancy, with the majority of resources focusing on the antenatal period. NHS preconception care in the UK broadly falls within the remit of primary care and sexual health services [11]. Women planning pregnancy are often a difficult to reach group and are more likely to engage with health services once they become pregnant rather than before. Moreover, preconception care has been reported by primary care providers as being constrained by time and resources as well as competing with other preventative care [12]. Therefore, the first barrier to intervention is identifying women planning pregnancy.

Trials of interventions to improve health before conception are few [13] and use an unselected approach in targeting the general preconception population. Targeted personalised intervention in higher risk women planning pregnancy may be a more efficient and beneficial approach. Through an online recruitment process, this study will evaluate a novel approach to both identification of women planning pregnancy and those most at risk and examine whether a targeted intervention will improve health behaviours and markers of metabolic health.

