### Study design

This is a single-arm feasibility trial. A flow diagram is shown in Fig. 1.

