### Study sample size

The sample size for the feasibility study is based on our objective to estimate the rate of participation of eligible women into the study. This study will recruit 55 women planning pregnancy. If we identify 110 eligible subjects, we will be able to estimate a participation rate of 50% to within a 95% confidence interval of ± 10% [15].

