### Follow-up assessment

The follow-up assessment will include the online health questionnaire and a blood sample at the end of the 12-week intervention.

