### Outcomes

*Change in self-report health behaviours to include:*
Weight/BMIDietary intakePhysical activity levelsSmoking statusAlcohol consumptionSupplementation with folic acid 400 μg/5 mg, vitamin D 10 μg*Change in biomarkers of metabolic health to include:*
Lipid profileHbA1cNutritional biomarkers including vitamin D, folate, vitamin B_12_, ferritin*Feasibility and process evaluation to include:*
The efficiency of the online recruitment system.Recruitment and retention:
Proportion of women who are eligible to take part in the intervention.Time to recruit 55 women.Loss to follow-up.Adequacy of 3-month timeframe to facilitate change in health behaviours and metabolic health.Dose delivered and dose received (the proportion of intended intervention received).Acceptability (if the intervention including online health assessment, home blood test kit, health coaching, intervention materials were well received by participants). Participating women will be asked to complete a digital questionnaire where they rate acceptability of the intervention components on a Likert scale.

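### The Discussion says pre-post change in a single arm will determine whether the strategy can improve health; without a comparator it can only describe change

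*Protocol article*

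**What the plan says.** The Discussion states what the before-and-after comparison is for: it "will determine whether this strategy can improve health in high risk women in the preconception period". The Background says, less firmly, that the study will "examine whether a targeted intervention will improve health behaviours and markers of metabolic health".

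The design is fixed under Study design: "This is a single-arm feasibility trial". Follow-up assessment gives one repeat of the online questionnaire and "a blood sample at the end of the 12-week intervention". The Analysis section plans linear and logistic regression of change with adjustment, and names no comparison group of any kind.

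Under Study sample size, "This study will recruit 55 women planning pregnancy", a number "based on our objective to estimate the rate of participation of eligible women into the study".

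The Study aim and Study objectives are more modest. They assess the feasibility of online recruitment, look at behaviours and biomarkers after the programme, measure change, and use the data to plan a randomised controlled trial.

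**The concern.** Determining whether a strategy can improve health is a causal conclusion. It needs some estimate of what would have happened to these women over the same 12 weeks without the programme, and the protocol supplies none. No analysis plan could add one by regression adjustment within a single arm, so this is not a detail left to a document we have not seen.

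The women are recruited because they are planning a pregnancy, have used a preconception tool and have agreed to take part. Some may well improve their habits without coaching. If the Discussion sentence guides the final report, change from all causes could be presented as a benefit of the programme. The protocol would also be claiming to settle a question that its own objectives leave to a later randomised trial.

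**Working it through.** **1. The plan's own figure.** Study sample size says: "If we identify 110 eligible subjects, we will be able to estimate a participation rate of 50% to within a 95% confidence interval of ± 10" percentage points. With p = 0.5 and n = 110, the half-width is 1.96 × √(0.5 × 0.5 / 110) = 1.96 × 0.0477 = 0.093, or ±9.3 points. The exact (Clopper-Pearson) interval is 40.3% to 59.7%, or ±9.7 points. Both are within ±10, so the figure reproduces. It concerns the participation rate only; the section gives no effect size, SD, power or significance level for change in health.

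**2. What the mean change contains.** With one arm measured twice, the expected observed change is:

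programme effect + background change + reporting bias + regression to the mean + selection of those followed up.

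The study yields one estimate of this sum for each outcome and cannot separate the terms. The protocol itself shows why the last four need not be zero:

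- *Background change:* women are invited after using a planning-for-pregnancy tool (Participant recruitment).
- *Reporting bias:* the first outcome group is headed "Change in self-report health behaviours to include", and the women answering know they are being coached.
- *Regression to the mean:* entry requires a BMI above a threshold (Inclusion criteria), and weight/BMI is a change outcome (Outcomes). This is possible rather than certain, because eligibility is screened on a separate questionnaire before the baseline one.
- *Selective follow-up:* loss to follow-up is itself listed as an outcome.

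**3. Precision of the change.** The 95% half-width for a mean change, in SDs of the change score, is t(0.975, n−1)/√n. For 55 women it is 2.005/√55 = 0.27. For 44 completers (20% loss, assumed) it is 2.017/√44 = 0.30. That interval covers change from all causes.

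**4. Illustration.** The documents give no drift or SD, so a range is assumed. Let the true programme effect be zero and let scores drift by d SDs of the change score for other reasons. The probability that a two-sided 5% paired t-test declares a change follows from the noncentral t distribution with noncentrality d√n:

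| Drift d (assumed) | 55 women | 44 completers |
|---|---|---|
| 0 | 0.05 | 0.05 |
| 0.1 | 0.11 | 0.10 |
| 0.2 | 0.31 | 0.25 |
| 0.3 | 0.59 | 0.49 |
| 0.5 | 0.95 | 0.90 |

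At each non-zero drift the probability is higher with 55 than with 44. More women in one arm would make the misreading more likely, so the missing comparator is the problem and not the sample size.

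**5. Side by side.** The Study aim and objectives speak of examining and measuring change and of informing a randomised trial. The Discussion speaks of determining whether the strategy can improve health. Only the first fits the design.

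**The case against.** The strongest reply is that this is one sentence in a Discussion. The operative text (aim, objectives, abstract, design label) is modest. The Analysis section sets no efficacy hypothesis, significance level or success criterion, and saying that a strategy *can* improve health is softer than saying it does. This stands as a limit on the point: the fault is in the stated inference, not in what will be done. It does not rescue the sentence, since a promise to determine whether improvement can occur is still a promise to settle the question.

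It is also fair that attrition is partly handled: the Analysis section plans to attempt follow-up of everyone, assess the type of missing data and run sensitivity analyses. That may reduce the selection term but leaves the others.

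Several stronger readings are tempting, and the documents do not support them:

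- *That the design or the sample of 55 is wrong.* The study is openly a feasibility trial, and 55 of 110 gives the precision claimed.
- *That the outcomes are mostly self-reported.* The Outcomes section lists six self-reported items (weight/BMI, diet, activity, smoking, alcohol, supplements) and six laboratory ones (lipids, HbA1c, vitamin D, folate, vitamin B12, ferritin).
- *That free supplements and referral of abnormal results are rival explanations.* Both are part of what participants are offered (Baseline assessment, Health coaching). The sentence concerns the strategy, not coaching alone.
- *That the later trial would be sized on the observed change, or replaced by this study.* No text says so.
- *That false-positive findings can be quantified.* The protocol states no 5% tests of change. Illustrative p-values are fragile: by an exact McNemar test, 6 women starting a supplement unprompted and none stopping give 2 × 0.5⁶ = 0.03, but a single stopper raises this to 2 × (1 + 7)/2⁷ = 0.125.

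**Conclusion.** Wrong as written. The Discussion sentence, and more weakly the one in the Background, states an inference that a single-arm before-and-after study with no comparator cannot deliver and that the protocol's own aim and objectives do not claim.

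That conclusion rests on the documents alone and needs no assumed figure. The probabilities in the table depend on the assumed drift, on a paired test the protocol does not name and, in the last column, on an assumed 20% loss. They show only that modest change from other causes could often be taken for benefit. How large that change would be in these women is unknown.

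**What to change.** In the Discussion, replace the sentence with wording such as: *Within-woman change after the intervention will be described with 95% confidence intervals to inform the outcome and design of a randomised trial; it will not be interpreted as an effect of the intervention.*

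In the Background, replace the clause on whether the intervention will improve behaviours and markers with one saying that the study will *describe change after a targeted intervention*.

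Both edits bring the text into line with the Study aim and Study objectives. Recruitment, data collection, sample size and the planned regression stay as they are. The only cost is a less ambitious stated conclusion.

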## Data Availability

Not applicable.

## Abbreviations

UK: United Kingdom
NHS: National Health Service
LMUP: London Measure of Unplanned Pregnancy
BMI: Body mass index
GDM: Gestational diabetes mellitus
